### Study regions and populations

During the study, data will be collected from multiple regions and populations targeted by the expanded community-based 4-level intervention. This protocol (version 1.1, dated 24.10.2024) has been registered in the ISRCTN registry under number ISRCTN10521127, registered 14/11/2025¸ https://www.isrctn.com/ISRCTN10521127).

### Regions

Each participating country selected a region which was feasible and had a suitable context for implementing a large-scale community intervention. A control region was chosen to match as closely as possible the characteristics of the chosen intervention region in terms of size, level of urbanisation, and sociodemographic characteristics, to minimise selection bias. Baseline sociodemographic and mental health indicators will be collected for both regions to assess comparability and to adjust for pre-existing differences in the analyses. Population sizes were matched as closely as feasible, ranging from approximately 117,538–350,000 inhabitants across the five participating countries (see Table 1).

**Table 1 pone.0352598.t001:** Overview of intervention and control sites.

Country	Intervention area (Number of inhabitants)	Control area (Number of inhabitants)
Albania	Central Tirana (350,000)	Elbasan (252,719)
Estonia	Mustamäe & Haabersti (117,538)	Lasnamäe (119,092)
Greece	Thessaloniki municipality (324,766)	Larissa (144,651)
Ireland	Limerick City & County Council (209,536)	County Galway (277,737)
Spain	Santa Coloma de Gramenet (119,195)	Sant Marti (242,752)

### Populations

The 4-level intervention is aimed at four main populations: Level 1 – General Practitioners and other primary healthcare providers; Level 2 – the general population, including the five vulnerable groups; Level 3 – community gatekeepers who work with the general population and the five vulnerable groups (e.g., police officers, social workers, teachers, youth workers, carers in geriatric settings, religious leaders, pharmacists); and Level 4 – people with depression and their families.

### Vulnerable groups

Within the scope of this project, the vulnerable groups are defined as per the following definitions: 1) **Young people** are defined as those between the ages of 15 and 24 years [48]; 2) **Older people** are defined as 65 + years [49]; 3) **Long-term unemployed** are defined as people who have been unemployed for twelve months or more [50]; 4) **Migrants/refugees**: a migrant is defined as someone who changes his or her country of usual residence, irrespective of the reason for migration or legal status [51], while a refugee is defined as someone who is unable or unwilling to return to their country of origin owing to a well-founded fear of being persecuted for reasons of race, religion, nationality, membership of a particular social group, or political opinion [52]; 5) **People with an existing mental disorder** include all people who have a current or previous diagnosis of depression or any other mental disorder, according to the Diagnostic and Statistical Manual of Mental Disorders or International Classification of Diseases [53,54], prior to the beginning of the trial. However, the definitions of the vulnerable groups provide a framework for the development of the project but are to be applied in a flexible and pragmatic way, and as there is a concurrent focus on the general population, no one is excluded from the project for not strictly meeting one of the aforementioned definitions.

In order to ensure that the adaptations to the vulnerable groups are trialled thoroughly in the intervention, each vulnerable group is a specific focus for at least three of the five intervention countries, as can be seen in Table 2.

**Table 2 pone.0352598.t002:** Vulnerable groups as a focus for the intervention by country.

	People with lived experience of mental disorder	Young people	Elderly	Unemployed	Migrants/Refugees
**Albania**	X	X	X		
**Estonia**	X	X		X	X
**Greece**	X	X	X		X
**Ireland**	X	X	X	X	
**Spain**	X			X	X

### Intervention and materials

The COMBINA project combines the EAAD community-based 4-level intervention for preventing suicide and reducing depression with innovative resources for improving wellbeing, and tailors the intervention towards the general population and the five identified vulnerable groups.

### Co-creation

A distinguishing feature of COMBINA is its participatory and co-creation approach, ensuring that the public and those affected by depression are involved in the design, or conduct, or reporting, or dissemination plans of this research. Co-creation ensures that intervention components are culturally and contextually relevant, fostering ownership and sustainability within each implementation site. Through iterative engagement with co-creators who represent the identified vulnerable groups and local stakeholders, the intervention is adapted to reflect the priorities and realities of local communities. Evidence increasingly supports co-creation as a mechanism that enhances feasibility, acceptability, contextual fit, and sustainability of health and mental-health interventions [22,55,56]. Within COMBINA, co-creation is embedded across all stages, from design to delivery and evaluation, representing both a methodological innovation and an implementation strategy.

### Materials

Materials have been developed for each of the four EAAD intervention levels: 1) Primary health care, 2) General population, 3) Community facilitators, 4) Affected individuals’ and their relatives. To ensure synergistic effects, it is essential that activities across all four levels are implemented simultaneously [57]. Each national team will adapt the training content to cultural and system contexts while maintaining core evidence-based elements of the EAAD model. An overview of the materials can be seen in Fig 3.

**Fig 3 pone.0352598.g003:**
[figure not shown]
Overview of intervention materials per level.

Level 1: Training for General Practitioners and Primary Care Providers. As part of the COMBINA intervention, comprehensive training programs were developed for General Practitioners (GPs) and other primary care professionals who treat depression depending on the local context, such as nurses and psychologists. These programs aim to enhance healthcare professionals’ capabilities in diagnosing, managing, and treating depression and suicidal behaviour, particularly among the identified vulnerable populations through appropriate curriculum on knowledge, attitudes and clinical skills. These trainings were crafted to ensure they meet the needs of patients affected by depression and suicidality accessing GPs and other healthcare professionals in the different regions. The trainings last 4–5 hours, with a strong practical component in practising skills learnt. Each country will decide, depending on local structure, whether to accredit the trainings. Trainings will be held by experienced psychiatrists, previously trained by the COMBINA team in specialized Train-the-Trainer (TTT) workshops.

Additional materials include informative leaflets outlining training content, objectives, and participation procedures, and handouts reinforcing key concepts and offering practical guidance during and after the training.

Level 2: Awareness Campaigns. A series of public awareness campaign materials have been co-developed with co-creators to enhance mental health literacy, increase recognition of depressive and subclinical symptoms, reduce stigma, and encourage help-seeking behaviour. These materials have been carefully designed, through engagement with co-creators, to be culturally sensitive, engaging, and easily understandable, drawing on evidence-based communication models for mental health promotion. Non-clinical symptoms were described as “common reactions to life adversities” to normalise these experiences and reduce stigma. This approach aligns with health literacy principles [58], simplifying complex medical language and making it easier for people with varying levels of education to understand and act on early signs of distress.

The materials, which can be seen in more detail in Fig 2, combine several complementary formats, including posters, flyers, fact sheets, and short promotional videos. Together, these materials aim to deliver clear, consistent messages across multiple channels, reaching different segments of the population and aiding both information provision and help-seeking. They are designed as a coherent package, combining concise visual messages, informative written content, and interactive elements. Posters and videos convey core messages in a simple and memorable way, while flyers and fact sheets offer more detailed information and practical advice. Visual identity elements, such a sprout symbol representing “You’re not alone,” are used consistently across formats to increase recognisability and reinforce key messages. The campaign also encourages people, especially young audiences, to share the sprout symbol on social media and messages as a simple act of solidarity and support.

To further promote mental wellbeing and broaden the reach of the intervention, the project has developed a free and openly available internet resource, the “iFight4WellBeing” website. This website has been developed in accordance with the four components of mental health literacy [59,60], providing an accessible, evidence-based online resource that addresses simultaneously subclinical symptoms and broader mental health concerns. The tool complements the community campaign and training activities by offering self-directed guidance and practical exercises in multiple languages. The content is divided into sections: understanding symptoms, a well-being assessment using the Patient Health Questionnaire-4 [61], a 4-week activity planner [62], physical exercise routines [63,64], guidance on sleep regulation [65], relaxation exercises [66,67], and guidance on when to seek professional help.

Level 3: Community Facilitators. Training programs have been developed for community facilitators to enhance awareness, identification, and management of depression and suicidality across different professional sectors. The curriculum builds on the evidence-based EAAD training materials and was adapted through expert consultation and co-creation with national partners to ensure cultural and contextual relevance. The trainings aim to build confidence in recognising signs of distress, initiating supportive conversations, and referring individuals to appropriate services. Content and format were adapted to the specific professional roles and working environments of each group, ensuring relevance and feasibility. Targeted groups included teachers, pharmacists, counsellors, social workers, geriatric caregivers, journalists, police, and clergy, among others. The training lasts for 4–5 hours and is delivered by a mental health specialist, such as a psychiatrist or psychologist.

Level 4: Patients, High-Risk Groups, and Relatives. Psychoeducational materials have been developed to support both patients and their families in managing depression, as can be seen in Fig 2. These include a fact sheet on depression, an information leaflet for family members, and an Emergency Card with contact details for local emergency services and personal emergency contacts.

Furthermore, patients with mild to moderate depression may be referred to a guided online self-management tool for people with mild to moderate depression: the iFightDepression® tool [68,69]. The iFightDepression® tool is part of the EAAD materials and is designed for use by patients with mild to moderate depression, who are referred by trained primary care professionals, and who guide the patient’s use of this self-management tool, based on cognitive behavioural therapy techniques. Referral criteria include: (1) age ≥ 15 years (or younger if deemed appropriate), (2) mild to moderate depression (clinician-assessed), (3) access to internet and email, and (4) informed consent provided. Exclusion criteria are: age < 15 years (unless locally permitted), severe depression, acute suicidality, or current substance abuse.

Cultural Adaptation and Translation. Materials have also been adapted to address the specific needs of each region’s local context and the five vulnerable groups. These adaptations were informed by stakeholder input and co-creation activities to ensure relevance. All materials are translated into the local regional languages: Albanian, Estonian, Greek, Spanish and Catalan. Translations have been validated by native speakers familiar with local mental health contexts, and a translation kit was developed to ensure consistency of key terms, phrases, and concepts across all materials.

All materials have also been translated and culturally adapted for major migrant groups in the participating regions, including the languages Arabic, Chinese, French, Lithuanian, Polish, Russian, Ukrainian, and Urdu. The adaptation process followed a structured framework combining forward translation, expert review, and validation by bilingual mental health professionals to ensure both linguistic accuracy and cultural appropriateness. Key terminology and core messages were standardised across languages to maintain consistency while allowing flexibility for local nuances. For older adults, printed materials have been provided with larger fonts and less text, including paper versions of the iFight4WellBeing resources to ensure accessibility for individuals with limited digital literacy or without digital access. For young people, materials were made visually more engaging with simplified language and age-appropriate vocabulary. Messages have been refined to align with local perceptions and cultural norms.

Regular bi-weekly meetings across countries will take place throughout the intervention period, to collaborate on how the intervention is being delivered in each context and share best practise.

### Implementation process

#### Data collection.

Participant recruitment and data collection for this trial began 24/09/2024 and will be completed by 31/12/2027. Participant recruitment will be completed by 31/01/2027, and data collection will be completed by 31/12/2027. Results will be provided by 31/03/2028. Recruitment began at different timepoints in the countries depending on when ethical approval was received. Recruitment began on 24/09/2024 in Greece, on 01/10/2024 in Estonia, on 07/10/2024 in Albania, on 12/11/2024 in Spain, and on 27/11/2024 in Ireland. The completion point for data collection is the same in all countries: 31/01/2027. Quantitative and qualitative data will be collected to support the outcome, process, and economic evaluations of the COMBINA intervention, as illustrated in Table 3. Please see Fig 4 for an overview of the timeline of the implementation process and different aspects of data collection. To guide the selection of indicators and measures, an Implementation Research Logic Model was developed for the EAAD community-based 4-level intervention and its implementation [75]. This model provides a detailed and comprehensive mapping of: determinants influencing implementation, implementation strategies employed, mechanisms of action, implementation outcomes, and clinical outcomes. An overview of this logic model is available in Supporting Information S2 File.

**Table 3 pone.0352598.t003:** Overview of indicators used for the data collection.

Indicator category	Indicator	Data source	Timing of data collection	Where collected
Outcome	Rates of completed suicide	Official statistics from responsible authorities in intervention and control sites	Retrospective and prospective rates from the period 2018–2026	Intervention and control regions
	Rates of hospitalisations due to suicide attempts	Medical records from hospitals in intervention and control sites	Rates from the period 2018–2026	Intervention and control regions
	Knowledge and attitudes related to depression, help-seeking, wellbeing, and symptoms of depression/anxiety	Validated surveys^a-d^ among general population in intervention and control sites	Before and 24 months after implementation	Intervention and control regions
	Competencies of professionals (Level 1 and Level 3 trainings)	Online validated survey^e,f^	Before and immediately after each training session	Intervention regions only (not applicable to control regions)
	Symptoms of depression in iFightDepression tool users	Online validated survey^g^ via iFightDepression tool (no control group)	At registering and 6 weeks later	Intervention regions only (not applicable to control regions)
Process	Reach of the intervention	Monitoring instrument and 4-level intervention tracker completed by research officers	During the 2-year implementation of the intervention	Intervention regions only (not applicable to control regions)
	Adoption, implementation, sustainability of the intervention	Interviews with research officers	After 24 months	Intervention regions only (not applicable to control regions)
	Adoption, implementation, sustainability of the intervention	Focus groups with stakeholders	After 24 months	Intervention regions only (not applicable to control regions)
	Satisfaction and acceptability of professionals (Level 1 and Level 3 trainings)	Online bespoke survey	Immediately after each training session	Intervention regions only (not applicable to control regions)
	Reach of the public campaign	Survey among general population (campaign awareness)	After 24 months	Intervention and control regions
	Reach of the iFightDepression tool	User data from iFightDepression tool and iFight4Wellbeing website	After 24 months	Intervention regions only (not applicable to control regions)
	Acceptability of the iFightDepression tool	Online survey among iFightDepression tool users	6 weeks after registration	Intervention regions only (not applicable to control regions)
	Acceptability of the iFightDepression tool	Online survey among iFightDepression tool guides	After 24 months	Intervention regions only (not applicable to control regions)
	Acceptability of the iFightDepression tool	Focus groups with guides of iFightDepression tool users	After 24 months	Intervention regions only (not applicable to control regions)
Cost	Direct costs of the intervention	Project cost tables, monitoring instrument, and exchanges with research officers	During the 2-year implementation of the intervention	Intervention regions only (not applicable to control regions)
	Costs of health care use and other resources used due to an (attempted) suicide	Estimates from literature, hospital data and expert opinion	Not applicable	Intervention and control regions
	Productivity losses due to an (attempted) suicide	Estimates from the literature, hospital data and expert opinion	Not applicable	Intervention and control regions

Key. ^a^ Depression Stigma Scale (DSS) [70]; ^b^ Attitudes Toward Seeking Professional Psychological Help-Short Form (ATSPPH-SF) [71]; ^c^ World Health Organisation – Five Wellbeing Index (WHO-5) [72]; ^d^ Patient Health Questionnaire 4 (PHQ-4) [61]; ^e^ Revised Depression Attitude Questionnaire (R-DAQ) (Haddad et al., 2015); ^f^ Literacy of Suicide Scale (LOSS) [73]; ^g^ Patient Health Questionnaire-9 (PHQ-9) [74].

**Fig 4 pone.0352598.g004:**
[figure not shown]
Timeline of the implementation process.

### Outcome evaluation

The outcome evaluation will primarily focus on **changes in attempted suicide rates**, operationalised as hospitalisations for intentional self-harm, comparing intervention and control regions over the 2-year implementation period. Monthly hospitalisation data for intentional self-harm will be retrospectively extracted from hospital records covering September 2019 to August 2026, from hospitals serving residents of the intervention and control regions and agreeing to provide data. **Suicides**, including deaths of undetermined intent, will be analysed as a **key secondary outcome**. Annual suicide mortality data will be obtained from national statistical offices for the years 2018–2026 and expressed per 100,000 population by gender.

Other secondary outcomes include changes in public knowledge and attitudes toward depression and its treatment, and mental wellbeing. These will be assessed through general population surveys conducted in both intervention and control regions at baseline and 24-month follow-up, with samples of 500 residents per region. The chosen sample size is consistent with earlier large-scale evaluations of the EAAD multi-level intervention [76], which successfully used regional samples of approximately 500 respondents to detect meaningful changes in depression stigma, attitudes toward help-seeking, and awareness of campaign activities across intervention and control regions. Replicating this sampling approach ensures sufficient power to detect small-to-moderate changes in our outcomes. The samples are stratified by age and gender, following predefined quota for the target population, and recruited through a mix of face-to-face interviews, telephone interviews, and online surveys. Surveys were carried out by external accredited market research agencies, to improve methodological robustness and reduce selection bias. The survey includes sociodemographic and health-related questions, and four validated scales. Below, the English language versions of the scales are described. Validated translations were used for Albanian, Estonian, Greek, and Spanish, and where no validated scale was available, a back translation process was used.

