## Abstract

Depression and suicide are leading public health problems requiring complex multilevel interventions. This study protocol details the COMBINA trial, which expands the evidence-based European Alliance Against Depression (EAAD) Community-Based 4-level intervention to also focus on improving wellbeing and tailored to five groups with increased vulnerability to depression: young people, older people, migrants/refugees, the long-term unemployed, and people with an existing mental health condition. In this prospective, non-randomised controlled trial, the COMBINA project will be newly implemented during a 24-month period, from late 2024 to late 2026, in five regions in Albania, Estonia, Greece, Ireland, and Spain. These regions will be compared to five control regions in the same countries, chosen to reflect a similar context, size, and sociodemographic characteristics. Main outcomes are a comparison between the intervention and control regions in the rates of deaths by suicide and hospitalisations for suicide attempts and the levels of wellbeing, depressive symptoms, anxiety symptoms, depression-related stigma, and willingness to seek psychological help in the general population. A process evaluation and economic evaluation will also be conducted. This intervention protocol also details the steps taken to promote successful implementation across a range of different cultural and regional contexts, with challenges including different existing mental health resources and differing capacities for the population to use digital tools. The COMBINA project includes co-creation, whereby materials and implementation strategy were designed with people from the vulnerable groups. The trial is funded by the European Union (grant agreement no. 101080651 and carried out according to the Declaration of Helsinki. Ethical approval has been obtained in all participating countries. The results will be published in peer-reviewed academic journals, presented at scientific meetings and disseminated through COMBINA stakeholders, with participation from the co-creators. This trial protocol (version 1.1, 24/10/2024) was registered in the ISRCTN registry (ISRCTN10521127) on 14/11/2025 (https://www.isrctn.com/ISRCTN10521127).

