### Ethics

The study was conducted according to the guidelines of the Declaration of Helsinki. The trial will be carried out at all times in strict accordance with the principles of voluntariness, confidentiality and non-harm. Ethical approval was received in each participating country, from the Ethical Committee of the Ministry of Health, Albania (No. 6653, date. 10.09.2024), the Human Research Ethics Committee of the National Institute for Health Development in Estonia (Decision No. 1372, date 19.09.2024), the Ethics in research committee of the Psychology department of the University of York Europe Campus in Thessaloniki (No. 1078, dt 16.07.2024), the Social Research Ethics Committee (SREC) Log No: 2024−227 (date: 29.11.2024; population survey) and Log No: 2025−015 (date: 27/02/2025; trainings) in Ireland, and the Drug Research Ethical Committee (CEIm) of Hospital del Mar in Spain (2024/11534/I; date 06/11/2024). All participants, where data is collected, receive information about the study and provide informed consent before participating. For the evaluations of L1 and L3 training participants, and for patients using the online iFightDepression tool, informed consent was provided by clicking on the box in the electronic form. This format for informed consent was also used for all the general population survey participants in Greece and Albania, and for those responding to the survey online in Estonia, Albania, and Spain. For phone and face-to-face interviews, informed consent was provided verbally in these countries. Verbal consent was witnessed by the evaluator and recorded in the tool, and in Spain voice recordings were also taken of the informed consent. No data was collected from any minors during the course of this study.

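### The hospital series for the primary outcome ends in August 2026, short of the 24-month implementation period it is meant to cover, and its window contradicts Table 3

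*Protocol article*

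**What the plan says.** The Outcome evaluation section of the protocol article makes attempted suicide, measured as hospitalisation for intentional self-harm, the primary focus, "comparing intervention and control regions over the 2-year implementation period". The data source is fixed in the next sentence: "Monthly hospitalisation data for intentional self-harm will be retrospectively extracted from hospital records covering September 2019 to August 2026".

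Three other places bear on that window:

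- The Abstract says the project is "newly implemented during a 24-month period, from late 2024 to late 2026".
- Table 3 gives the hospitalisation indicator as "rates from the period 2018–2026", the same years as for suicide deaths.
- The Data collection section dates the start of recruitment by country: "Recruitment began on 24/09/2024 in Greece, on 01/10/2024 in Estonia, on 07/10/2024 in Albania, on 12/11/2024 in Spain, and on 27/11/2024 in Ireland". Table 3 times the general population survey as "Before and 24 months after implementation", so the baseline survey precedes launch.

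The text gives no launch date for any country. Fig 4, the implementation timeline, is not reproduced in the copy reviewed. The Statistical analysis section lists interrupted time series, Poisson regression and mixed models, but names no intervention start month for the hospital series.

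**The concern.** A series that stops in August 2026 cannot supply a full 24 months after launch if launch came in late September 2024 or later. The missing months fall at the end of implementation and differ in number between countries, so the five pairs of regions would contribute unequal follow-up to a comparison described as two years in all of them.

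The article also publishes two incompatible windows for its primary outcome, which is the primary economic outcome as well. They differ at both ends, so they change the length of both the pre-period and the post-period in an interrupted time series. If this stays unresolved until the outcome data are in hand, the choice between them could be made after the results are known. A later analysis plan cannot repair the shorter window unless the extra months are requested from the hospitals.

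**Working it through.** **Step 1: the plan's own figure.** The stated comparison period is 2 years, or 24 months. September 2019 to August 2026 is 7 × 12 = 84 months. The last 24 of these run from September 2024 to August 2026, leaving 60 before them. The window therefore yields 24 post-launch months only if every country launched on 1 September 2024. No date in the article gives that start.

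**Step 2: coverage by country.** Assumption: the earliest possible launch is the stated recruitment start. This follows from Table 3 if the baseline survey did precede implementation, but the article does not call these launch dates.

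Coverage = days from start to 31/08/2026 inclusive ÷ 30.4375. Shortfall = 24 − coverage.

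| Country | Assumed start | Days | Coverage (months) | Shortfall (months) | 24 months reached |
|---|---|---|---|---|---|
| Greece | 24/09/2024 | 707 | 23.2 | 0.8 (3%) | 24/09/2026 |
| Estonia | 01/10/2024 | 700 | 23.0 | 1.0 (4%) | 01/10/2026 |
| Albania | 07/10/2024 | 694 | 22.8 | 1.2 (5%) | 07/10/2026 |
| Spain | 12/11/2024 | 658 | 21.6 | 2.4 (10%) | 12/11/2026 |
| Ireland | 27/11/2024 | 643 | 21.1 | 2.9 (12%) | 27/11/2026 |

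Total: 3,402 days ÷ 30.4375 = 111.8 region-months, against 5 × 24 = 120 planned. That is 93%, a loss of about 7%, with mean coverage of 22.4 months. Each month by which launch followed recruitment adds a further month of shortfall in that country.

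**Step 3: the two windows side by side.** Reading Table 3 as whole calendar years and splitting at September 2024:

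| Source | Months before September 2024 | Months from September 2024 | Total |
|---|---|---|---|
| Outcome evaluation (Sep 2019–Aug 2026) | 60 | 24 | 84 |
| Table 3 (Jan 2018–Dec 2026) | 80 | 28 | 108 |

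The Table 3 window would cover 24 months in every country on the dates in Step 2. The Outcome evaluation window covers it in none.

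**Step 4: a conditional calculation.** Suppose the analysis used a common start of 1 September 2024, which the article does not state. With *f* months after the true start and a constant rate ratio RR, the average over the nominal 24 months is [(24 − *f*) + *f* × RR] ÷ 24. For an assumed RR of 0.80:

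- Greece: (0.77 + 23.23 × 0.80) ÷ 24 = 0.806
- Ireland: (2.88 + 21.12 × 0.80) ÷ 24 = 0.824
- Mean of the five countries: 0.814

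On the same basis an assumed RR of 0.90 averages 0.907, and 0.70 averages 0.721.

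**The case against.** The strongest reply is that the problem is small and partly outside what an article must show. Recruitment dates are not launch dates, the timeline figure is unavailable, and the coding of the intervention period is usually left to the analysis plan. On the stated dates 93% of the intervention region-months are covered. No sample size or power is given for this outcome, so no loss of power can be calculated. All of that stands, and it limits the size of the point. It does not reconcile the two windows. Even as a loose list of calendar years, Table 3 includes 2018, which a series starting in September 2019 does not touch.

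Three stronger readings are tempting, and the article does not support them:

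- **That months before launch are counted as intervention time.** A reader might infer this because 84 splits neatly into 60 and 24. No breakpoint is stated, and the listed methods can use country-specific starts. The dilution in Step 4 is therefore conditional.
- **That stopping early biases the result toward no difference.** With a constant effect, a shorter series loses precision and causes no bias. Understatement needs an effect that grows with cumulative exposure. That is plausible for training and campaigns, but the article does not state it.
- **That Irish exposure began only with the ethics approval recorded as "Log No: 2025−015 (date: 27/02/2025; trainings) in Ireland".** The approval is labelled for trainings, and the Ethics section discusses consent in terms of evaluating trainees. Trainings make up two of the four levels, and nothing says the campaign or patient materials waited for it.

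A practical objection also has some force. The data depend on hospitals that agree to supply them, and the Discussion reports variable availability and quality. An extension, or a 2018 start, may not be possible everywhere.

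**Conclusion.** The concern holds in a limited form. As written, the hospital series for the primary outcome does not cover the 24 months over which the comparison is promised, and its window conflicts with Table 3 and the Abstract. With launch no earlier than recruitment, the shortfall is 0.8 to 2.9 months per country, about 7% of intervention region-months overall. It is larger if launches were later. The certain consequences are lost precision, unequal follow-up between countries and an unresolved choice of window. Bias is possible but not shown: it requires either an effect that builds over time or a common September 2024 start. Under the latter, an assumed rate ratio of 0.80 would average about 0.81. The size is modest. The point still merits correction because it concerns the primary outcome and the repair is simple.

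**What to change.** 1. State one window for the hospital series, identical in Outcome evaluation and Table 3.
2. Extend monthly extraction to the end of the 24th month after each country's documented launch. On the stated dates that means at least November 2026, and later where launch was later. Use the same calendar window for the paired control region.
3. Record each country's launch month and code the intervention start from it, so that no common start is implied.
4. Choose one series start, January 2018 or September 2019, and report which hospitals cannot supply the earlier months.
5. Reconcile the two end dates for data collection in the Data collection section, 31/01/2027 and 31/12/2027. Both fall after November 2026, so either accommodates the extension on the stated dates. A launch later than January 2025 would need data beyond the earlier date.

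The cost is a change of wording and a slightly later request to hospitals, which must agree to it. No new participants are needed.
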